#### Caseload midwives, non-caseload midwives and other key stakeholders

○ *A *questionnaire will be administered to all caseload midwives and non-caseload midwives near the beginning and at completion of the trial. In-depth interviews will also be conducted with all caseload midwives and a sample of non-caseload midwives and other key stakeholders, near the beginning of the trial and on completion. These will be audio-taped then transcribed verbatim.

○ Midwife retention rates for caseload midwives and non-caseload midwives will be estimated at baseline and post-trial to enable a comparison.

○ Logs of caseload midwives' time spent on their various work tasks will be collected for several one-month intervals throughout the trial.

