The impact of the caseload midwifery model on staff retention and attrition is unknown, but is another important issue for consideration in light of the fact that a 2002 review of the midwifery workforce in Australia concluded that there is a national shortage of midwives that is expected to increase over the next few years [17]. It is possible that the continuity inherent in caseload midwifery and potential for lower intervention childbirth would improve midwife satisfaction [18-21]; however studies in the UK and Australia have reported problems with the widespread implementation and organisation of models that promote continuity of carer. Issues for midwives include high and unsustainable workloads, personal costs (impinging on family life) [22,23]; and burnout and stress [24]. A caseload model in Sydney ceased operations in 2001 following "many stressors from within and beyond the partnership model" [[5], p34]. In response to these issues, some organisations have altered their approach, and moved from a caseload model to midwifery teams [25]. A 2000 review of continuity of carer models concluded that services should be organised in a way that aims to put less strain on midwives' lives [26]. Conflict between midwives working in new models and the staff in traditional models has also been reported [27,28]. Midwives in new models, or the new models themselves, may be seen as a threat by medical staff, in that the midwives may be taking on work otherwise done by them [21]. In a qualitative evaluation of a team midwifery model in Brisbane, midwives were surprised by the lack of support from other staff, both peers and administrators [27]. In two other trials it was reported that team midwives had to frequently respond to criticisms about their role or work practices [28]. In a setting of midwifery workforce shortages it is critical that the impact of new models of care is properly evaluated with regard to midwife job satisfaction, recruitment and retention.

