It is not clear whether continuity of carer per se is more important to women than consistent and personalised care, even if it is provided by a number of care-givers [26,48].

We plan to implement a caseload midwifery model under RCT conditions to evaluate its effect on the rate of caesarean section and on a range of significant secondary outcomes. This paper describes the trial protocol in detail.

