### Aims

This study aims to determine whether caseload (one to one) midwifery care for women at low risk of medical complications decreases the proportion of women delivering by caesarean section compared with women receiving 'standard' care. The primary hypothesis is that:

Women randomised to caseload midwifery care will have 5% fewer caesarean section births than women in standard care model, that is, 14% versus 19%.

Secondary aims of the study are to compare caseload midwifery and standard care with regard to differences in:

a) Maternal outcomes

- instrumental vaginal births, obstetric analgesia, perineal trauma, and induction of labour;

- postnatal depression;

- satisfaction with care;

- breastfeeding duration;

- smoking cessation.

b) Midwife outcomes (compared to midwives providing standard care)

- staff attrition from the model of care and the hospital;

- work satisfaction;

- burnout.

c) Costs and cost effectiveness

A final aim is to collect data on maternal and perinatal morbidity and mortality for inclusion in meta-analyses (the sample size will be insufficient to determine statistical differences). These include measures of perinatal morbidity and mortality and maternal mortality and morbidity.

Comprehensive process evaluation will be undertaken to explore sustainability issues and to assess intervention compliance.

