#### Data collection forms/software

- Background demographic questionnaire

- Two month questionnaire

- Six month questionnaire

- Medical/obstetric outcome collection form

- Daily recruitment figures form

- Excel workbook to track recruitment and record data related to population numbers, proportion approached and consented, and reasons for non-participation [53]

- Access database to track participants [50]

- Staff surveys at start and end of trial

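### Midwife burnout and satisfaction are scored only near the start and at completion, so the final comparison with standard-care midwives is conditional on not having left

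*Protocol article*

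**What the plan says.** All references are to the protocol article.

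- **Outcomes.** Aims lists three midwife outcomes, each to be compared with midwives giving standard care: "staff attrition from the model of care and the hospital", work satisfaction, and burnout.
- **Questionnaire.** The part of Data collection that deals with midwives and other stakeholders sets the timing: "questionnaire will be administered to all caseload midwives and non-caseload midwives near the beginning and at completion of the trial". Data collection forms/software agrees, listing "Staff surveys at start and end of trial" and no exit or interim staff form.
- **Interviews.** These are set "near the beginning of the trial and on completion". Adherence to protocols repeats the beginning and end for the intervention midwives.
- **Between the two points.** Task-time logs are kept for some one-month intervals, and monthly support meetings are held. Neither is described as measuring burnout or satisfaction.
- **Retention.** "Midwife retention rates for caseload midwives and non-caseload midwives will be estimated at baseline and post-trial to enable a comparison".
- **Setting.** The trial brings the model in: "We plan to implement a caseload midwifery model under RCT conditions". Background reports workload, stress and burnout problems in continuity models, and a Sydney caseload model that closed.

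**The concern.** A burnout score at completion exists only for someone who can still be surveyed then. Leaving is one of the outcomes, and Background treats burnout as a plausible problem of such models. A midwife who starts, becomes burnt out and leaves has at most a score from near the beginning, before sustained exposure. If she joined after the first survey she has none. Her replacement may be surveyed after short exposure and with no entry score. A midwife who leaves caseload but stays at the hospital may be counted at completion as a non-caseload midwife, which would put her score in the comparator.

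The retention measure has a related weakness. Retention in caseload posts cannot be estimated at baseline, because those posts do not exist until the trial creates them.

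At stake is whether the workforce results, which the protocol treats as important for sustainability, compare like with like.

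**Working it through.** **1. Length of the gap.** Timelines gives 24 months of recruitment and a further 14 months to complete data collection after the last woman is recruited. Completion is not dated more exactly, so the gap between surveys is at least about 24 months and at most about 24 + 14 = 38.

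**2. Size of the caseload group.** Recruitment of midwives to caseload states about 12 full-time midwives. Check against the protocol's own figures: 1004 women per arm (Sample size), 2 years of recruitment, 40 to 45 women per midwife per year (Background).

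- 1004 / 2 / 45 = 11.2
- 1004 / 2 / 40 = 12.6

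The stated figure is reproduced. If each post is one person, a single leaver is 1/12 = 8% of the group. The protocol allows part-time staff, so there may be more people than posts.

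**3. Effect of loss within one group.** Let f be the share of the starting midwives who leave and d the amount, in SD, by which leavers score worse than stayers.

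- Mean of the whole group = stayers' mean + f × d
- So the completion mean is too favourable by f × d

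**4. Effect on the planned comparison.** Both groups follow the same schedule, so

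- bias = (f × d in caseload) − (f × d in standard care)

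**5. Illustration.** The protocol gives neither f nor d. Assume annual attrition of 20% in caseload and 10% in standard care over 2 years, with d from 0.5 to 1.0 in both groups.

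- Caseload: f = 1 − 0.8² = 0.36
- Standard care: f = 1 − 0.9² = 0.19
- Bias = (0.36 − 0.19) × d = 0.17 × d, which is 0.085 at d = 0.5 and 0.17 at d = 1.0

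Other cases:

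| Loss, caseload v standard | d, caseload v standard | Bias in comparison (SD) |
|---|---|---|
| 36% v 19% | 0.5 v 0.5 | 0.085 |
| 36% v 19% | 1.0 v 1.0 | 0.17 |
| 36% v 36% | equal | 0 |
| 36% v 36% | 1.0 v 0.5 | 0.18 |
| 19% v 36% | 1.0 v 1.0 | −0.17 |

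Positive values flatter caseload. Equal loss removes the bias only if leavers' scores are also equally worse. If standard care loses more, the sign reverses.

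**6. Retention.** Aims has two forms of attrition. Retention at the hospital can have a baseline rate, including for midwives who later move into caseload, since posts are advertised internally first. Retention in caseload posts cannot, because the trial introduces them. A baseline versus post-trial contrast is therefore possible for the first form and not for the second.

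**The case against.** The strongest reply has five parts.

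- **Silence, not exclusion.** The survey goes to all caseload and non-caseload midwives, and former staff are not expressly excluded. A journal article may leave the handling of leavers to the full protocol. This stands in part: the text does not say that only those in post are surveyed. But the start-and-end timing is stated for the questionnaire, the interviews and the form list alike, so it is a fixed schedule. If former midwives are meant to be included, the article should say so, and a survey at the end is still not one at leaving.
- **Attrition would show the loss.** This stands. A reader might infer that midwives harmed by the model vanish from the trial and that the sustainability question would be answered wrongly. The document does not support that, because attrition is an outcome in its own right and would be read beside burnout. What is lost is narrower: leavers' burnout and satisfaction scores and, unless asked, their reasons.
- **The size.** A reader might take 2, 4 or 6 leavers out of 12, each 1 SD worse, and conclude that the burnout result is too favourable by 2/12 = 0.17, 4/12 = 0.33 or 6/12 = 0.50 SD. That is the shift in the caseload mean alone under an assumed gap. The aim is a comparison, and standard-care midwives leave too. Nothing in the document shows that caseload loses more; Background calls the impact on attrition unknown.
- **Noise.** With 12 midwives the standard error of a mean is 1/√12 = 0.29 SD, larger than the illustrated bias. True, though imprecision does not make a selective comparison sound.
- **Baseline retention.** A reader might infer that no baseline retention rate is possible at all. That holds only for retention in the model, as shown above.

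**Conclusion.** The point holds in a limited form. As written, burnout and satisfaction at completion are conditional on not having left, over a gap of at least 24 months, and no measurement is planned at exit. The comparison with standard-care midwives is biased only so far as loss or leavers' scores differ between groups: 0.085 to 0.17 SD under an assumed 36% v 19% loss with leavers 0.5 to 1.0 SD worse, and zero if both loss and leaver scores are equal. Direction and size are not known from the document. The baseline retention rate is unworkable for the caseload model but not for the hospital. These are secondary, non-randomised outcomes in a small staff group; the caesarean comparison and the other outcomes in women are unaffected. The change is worth making because it is cheap and exit scores are hard to recover afterwards.

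**What to change.** - **Measure at exit and entry.** In the staff data collection section and the list of forms, give the existing questionnaire to every caseload and non-caseload midwife on leaving the model or the hospital, and to replacements on entry.
- **Report both comparisons.** Present burnout and satisfaction with leavers' exit scores included, beside the completion-only comparison and the attrition result. Exit scores should not silently replace completion scores, because they reflect different lengths of exposure.
- **Classify movers.** Analyse midwives who move from caseload to standard care under their original model.
- **Attrition from the model.** Replace the baseline versus post-trial contrast with the proportion leaving, or time to leaving, over the same calendar window in both groups. A baseline hospital retention rate can stay as context.

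**Cost.** No new instrument: an existing form sent at more occasions, plus start and leave dates. The downsides are varying exposure at exit and the need for access to personnel records for non-caseload midwives. Informed written consent mentions only interviewed staff and caseload midwives, so that access would need to be cleared.

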#### Economic evaluation

○ Resource use data will be collected from the medical record following birth and from women's self-reported use of health care and other resources in the six months after birth, via the postal questionnaires at two and six months postpartum.

### Data coding

Data coding schedules have been devised for each survey questionnaire, and coding will be undertaken as the questionnaires are returned.

### Data management

#### Data storage

Data will be stored in locked filing cabinets in locked rooms and accessed only by the project coordinator and chief investigators. Computer files will be password protected and will be accessed only by the project coordinator and chief investigators. Data linking women's names and study ID will be kept on a separate database to women's questionnaires which will be identified by study ID only.

#### Data entry

Survey data will be entered by a professional data entry company then the files exported to an Access database [50].

Qualitative data entry: open-ended questions from the surveys will be entered by the project coordinator. Key informant interviews will be transcribed verbatim by an external professional transcriber. Analysis will be undertaken by members of the research team.

#### Data cleaning

Data cleaning for quantitative data will be undertaken using a variety of approaches including range and logical checks, first in Access [50] then again when the data is transferred to the statistical software package STATA [51].

### Data analysis

#### Quantitative analysis

This will be undertaken using STATA [51] and data will be collected to meet the CONSORT guidelines for reporting of randomised trials.

The first stage of analysis will check the comparability of participants allocated to the two groups. The intervention group will be compared with the standard care group by intention to treat analysis. Proportions of women having a caesarean section will be compared using chi-square tests and odds/risk ratios. Comparison of means will be undertaken for continuous variables using t-tests where data are normally distributed or medians compared using Mann-Whitney U tests otherwise. Ranked or Likert-type scales will be analysed using cumulative odds ratios. Where there are differences in baseline characteristics of the women in the two groups which might be associated with outcomes, an additional multivariate analysis will be carried out.

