## Methods/design

The study uses a two arm, unblinded randomised controlled design, stratified by parity, to compare caseload midwifery care with standard maternity care.

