### Sample size

Initial power calculations were based on the caesarean section rate for women who were low risk at booking at the Royal Women's hospital in 2005, i.e. 19%. It was hypothesised that the caseload model of care would decrease the caesarean section rate from 19% to 14%. In order to detect such a difference (with 80% power and 95% confidence) we needed 904 women in each trial arm. Allowing for 10% loss to follow up, 1004 women in each group were required, i.e. a total sample of 2008. This sample size also enables the detection of a range of other statistically significant differences to be detected for the major secondary outcomes, as shown in Table 1.

**Table 1 T1:** Power calculations with n = 904** in each arm

*Outcome*	*Standard care*	*Caseload*	*Power to detect specified difference*
	%	%	
Birth by caesarean section	19	14	80
Instrumental vaginal birth	10.6	6.6	84
Epidural analgesia	18	13	82
Intact perineum or unsutured laceration (increase)*	41.2	48.2	84
Intact perineum or unsutured laceration (decrease)*	41.2	34.2	86
3rd or 4th degree laceration* (would not miss this difference)	1.7	3.4	57
Induction of labour	27	21	84
Augmentation of labour	19	14	80
Exclusive breastfeeding at 6 months	8	12	79
Any breastfeeding at 6 months	53	63	99
Postnatal depression at 8 weeks	15	10	88
Postnatal depression at 6 months	15	10	88
Smoking at time of birth	15	10	88

*These estimations exclude caesarean births

** Allows for loss to follow-up

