### Intervention allocation

#### Randomisation procedure

The randomisation system in use for the trial was developed by the Australian National Health and Medical Research Centre Clinical Trials Centre . An Interactive Voice Response System (IVRS) activated by telephone will be used for randomising women to the two treatment arms of the trial (i.e. standard care and caseload midwifery care).

Randomisation will be undertaken using stratified permuted blocks of varying size, with randomisation stratified by parity (i.e. first or subsequent birth). For each woman, the system will assign the treatment in the next available sequential slot in the appropriate list of blocks.

When a woman agrees to enter the study the research midwife will complete a COSMOS study specific Trial Randomisation IVRS Worksheet with details that the system will request to complete the randomisation procedure (e.g. woman's full initials, parity and date of birth). Access to the IVRS is achieved by dialing a toll-free telephone number and navigating to the COSMOS trial via a menu system. The system is designed so that no woman can be randomised twice. A back-up system is in place in case of a system failure, via a nominated person at the Clinical Trial Centre. After completing all prompts the woman will be allocated a study number and treatment arm. The woman will be informed immediately of the randomisation outcome and further maternity care bookings arranged accordingly.

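### The primary caesarean comparison does not account for parity, the randomisation stratum; a parity-stratified analysis would be a small improvement at no cost

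*Protocol article*

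**What the plan says.** The protocol article describes the design under Methods/design as a "two arm, unblinded randomised controlled design, stratified by parity". Under Randomisation procedure the allocation uses "stratified permuted blocks of varying size, with randomisation stratified by parity (i.e. first or subsequent birth"). No other stratification factor is named.

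Under Quantitative analysis the primary comparison is set out in one sentence: "Proportions of women having a caesarean section will be compared using chi-square tests and odds/risk ratios". The strata are not mentioned. The same paragraph has one adjustment clause. It applies "Where there are differences in baseline characteristics of the women in the two groups which might be associated with outcomes", and in that case "an additional multivariate analysis will be carried out".

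The hypothesis under Aims is an absolute contrast: "Women randomised to caseload midwifery care will have 5% fewer caesarean section births than women in standard care model", given as 14% against 19%.

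**The concern.** Permuted blocks within parity hold the two arms nearly equal in their share of first births. Chance imbalance in parity therefore contributes almost nothing to the difference between arms. The ordinary chi-square variance still includes that contribution. If caesarean risk differs by parity, the standard error is too large, the test rejects less often than its nominal level under the null, and power already secured by the design goes unused.

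The adjustment clause does not close the gap. It depends on an observed baseline difference, and parity is the characteristic that the design keeps from differing. If the clause is triggered, the result is an additional analysis and not the primary one.

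At stake is a little precision on the primary outcome. The validity of the result is not in question.

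**Working it through.** **Inputs from the article.** Caesarean 19% (standard care) against 14% (caseload), 80% power, 95% confidence (read as two-sided 5%), 904 per arm, 1004 per arm after 10% loss (Sample size). Women with a previous caesarean or a planned elective caesarean are excluded (Exclusion criteria and the obstetric list).

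**Inputs assumed.** The share of first births and the caesarean rates by parity are not given. The main case takes 50% first births and lets first-birth risk be 1, 2, 3 or 5 times subsequent-birth risk, with the overall rates held at 19% and 14% and a common odds ratio across strata.

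**Step 1: the plan's own figure.** With mean proportion 0.165 and difference 0.05:

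n = [1.96·√(2·0.165·0.835) + 0.842·√(0.19·0.81 + 0.14·0.86)]² / 0.05² = 864 per arm.

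The continuity correction gives (864/4)·[1 + √(1 + 4/(864·0.05))]² = 904. This matches the article. Dividing by 0.9 gives 1004.4, against the stated 1004.

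**Step 2: power of the uncorrected chi-square with no parity effect.** The null standard error is √(2·0.165·0.835/904) = 0.01746. The standard error under the alternative is √((0.1539 + 0.1204)/904) = 0.01742. Power = Φ[(0.05 − 1.96·0.01746)/0.01742] = 81.8%. The 95% half-width is 1.96·0.01742 = 3.41 percentage points.

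**Step 3: variance removed by stratifying.** Under stratified allocation the real variance is the within-stratum average f·p₁(1−p₁) + (1−f)·p₂(1−p₂), where f is the share of first births. The crude test uses p(1−p) = 0.19·0.81 = 0.1539. The true size of the crude test is 2·[1 − Φ(1.96/√r)], where r is the ratio of the two.

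Example at three-fold risk: control rates are 28.5% and 9.5%. The within-stratum variance is 0.5·(0.285·0.715) + 0.5·(0.095·0.905) = 0.1449, so r = 0.941 and the size is about 4.3% (4.4% by simulation).

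**Step 4: results for a 50:50 mix, 904 per arm.** Type I error is from 200,000 simulated trials per scenario, except at ratio 1, where it is exact by formula. Power is by formula, and simulation agrees to within 0.3 points.

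| First/subsequent risk | Control rates (%) | Type I error, crude test | Power, crude → stratified | Half-width, crude → stratified (points) |
|---|---|---|---|---|
| 1 | 19.0 / 19.0 | 5.0% | 81.8 → 81.8% | 3.41 → 3.41 |
| 2 | 25.3 / 12.7 | 4.7% | 82.0 → 82.6% | 3.41 → 3.37 |
| 3 | 28.5 / 9.5 | 4.4% | 82.4 → 83.7% | 3.41 → 3.32 |
| 5 | 31.7 / 6.3 | 3.9% | 82.9 → 85.2% | 3.41 → 3.25 |

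The Cochran-Mantel-Haenszel test stays at about 5.0% in the simulated scenarios. Simulated coverage of the crude nominal 95% interval under the alternative is 95.3%, 95.5% and 95.9% at ratios 2, 3 and 5.

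**Step 5: other mixes.** With 40% to 70% first births and ratios 2 to 5, the risk-difference interval narrows by 0.8% to 6.2% and power rises by about 0.4 to 3 points. At ratio 8 the extremes are 8.9% and about 4 points.

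**Step 6: which measure gains.** At ratio 3 and a 50:50 mix, the log odds ratio has a standard error of 0.128 unadjusted and 0.132 conditional on parity. The conditional odds ratio is a different and more extreme quantity (0.680 against 0.694 here). Its interval does not narrow, although the test gains power.

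**The case against.** The case for leaving the plan alone is reasonable. The error is in the safe direction, the marginal risk difference and risk ratio are unbiased, and the crude test already has about 82% power against a stated 80%. The sentence never says that the analysis is unadjusted, and a separate analysis plan may bring parity in. All of this stands except the last part as a defence. The article names a specific method for the primary outcome, so an analysis plan that stratifies would have to be reconciled with it.

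Three stronger readings are tempting, and the document does not support them.

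- A reader might take parity to be an established strong predictor of caesarean birth in this population. The choice of parity as stratifier and the exclusion of previous caesarean make some effect plausible. The article gives no rates by parity, so its strength is unknown and may be modest.
- A reader might extend the point to instrumental birth, epidural, perineal trauma and augmentation. Table 1 gives no rates by parity for any of them, and the chi-square sentence names caesarean section only.
- A reader might say that ratios alone cannot answer a hypothesis about an absolute difference. The plan does compare the two proportions, so the difference can be read off. The lack of a named interval for it is a lesser reporting matter.

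**Conclusion.** The point holds as a minor efficiency issue. The design stratifies by parity, the stated primary analysis does not account for it, and the conditional adjustment clause is unlikely to bring it in. If parity is prognostic, the crude test is mildly conservative: about 4.7% to 3.9% true size for a 50:50 mix and risk ratios of 2 to 5, with 0.6 to 2.3 power points to be gained. If parity is not prognostic, the gain is zero. The direction is certain given a parity effect; the size depends wholly on the assumed mix and rates.

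It would be wrong to conclude that the trial is underpowered, that its result would be biased, or that false positives are inflated. None of these follows.

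**What to change.** State that the primary comparison is stratified by parity as randomised, regardless of the balance observed. Use a Cochran-Mantel-Haenszel test, report the Mantel-Haenszel risk difference with its 95% CI as the main estimate, and give the stratified risk ratio beside it. Keep the crude chi-square as a check. Do not rely on a parity-conditional odds ratio for the precision gain; if one is reported, label it as conditional on parity.

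The cost is a sentence or two of analysis wording. Parity is already entered for every woman at randomisation, so no new data and no change in sample size are needed. If a separate analysis plan already stratifies, bring the two texts into line.

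### Whether and how the supplementary adjusted analysis is done depends on chance baseline differences, so it can pass over balanced prognostic factors, including the stratification factor parity

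*Protocol article*

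**What the plan says.** All of the relevant analysis text is in the protocol article, under Data analysis, Quantitative analysis.

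- The order of work: "The first stage of analysis will check the comparability of participants allocated to the two groups".
- The main comparison, by intention to treat and with no condition attached: "Proportions of women having a caesarean section will be compared using chi-square tests and odds/risk ratios".
- The adjustment rule: "Where there are differences in baseline characteristics of the women in the two groups which might be associated with outcomes, an additional multivariate analysis" is to be done.

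The Randomisation procedure section describes a central telephone system using permuted blocks of varying size, "with randomisation stratified by parity (i.e. first or subsequent birth"). The Methods/design section says that the trial is unblinded and again names parity as the stratification factor. Parity is not named anywhere for the analysis.

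The Sample size section rests on an unadjusted comparison of 19% with 14%, at 904 women per arm before allowance for loss.

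**The concern.** The protocol does more than leave covariates to a later document. It states a rule, and the rule takes observed imbalance as the reason to adjust. With concealed central allocation, any baseline difference is chance. What makes a covariate worth including is how strongly it predicts the outcome, and that does not depend on whether it happens to differ between arms.

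Three things follow.

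- A strong predictor that balances is left out.
- Parity is the clearest case. Within each parity stratum the arms can differ only by what an unfinished block allows, so an imbalance trigger would almost never select it, although the design treats it as important enough to stratify on.
- Chance decides whether a second estimate of the primary outcome exists, and someone must judge after the fact which differences count. In an unblinded trial that discretion is better closed beforehand.

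At stake are some precision and some avoidable latitude, rather than the validity of the main test.

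**Working it through.** **1. The plan's own figure.** Inputs from the Sample size section: 19% versus 14%, 80% power, 95% confidence (two-sided 5%), equal arms.

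n = [1.960·√(2·0.165·0.835) + 0.842·√(0.19·0.81 + 0.14·0.86)]² / 0.05² = 864 per arm.

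With continuity correction, n' = (n/4)·[1 + √(1 + 4/(n·0.05))]² = 904. This matches the protocol. The sample size is thus built on the unadjusted two-proportion test. Dividing by 0.9 gives 1004.4, against the stated 1004.

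**2. How often chance fires the trigger.** The protocol gives no threshold and no list. Assume p < 0.05 and k independent variables that pass its condition of possible association with outcome. Then P(at least one) = 1 − 0.95^k:

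| k | 5 | 8 | 10 | 15 | 20 |
|---|---|---|---|---|---|
| P | 23% | 34% | 40% | 54% | 64% |

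For six variables the formula gives 1 − 0.95^6 = 26% at p < 0.05 and 1 − 0.80^6 = 74% at p < 0.20. The threshold largely decides whether a second model exists.

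**3. What the trigger gains or costs.** Simulation with 904 per arm and 4000 trials per setting. Assumptions not in the protocol: half first births, parity balanced by stratification, parity odds ratio 2 to 6, and six other binary covariates each with odds ratio 1.5.

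Power (%) for 19% versus 14%:

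| Parity OR, trigger | Chi-square | Parity only | Parity + six, fixed in advance | Triggered | Trigger fired |
|---|---|---|---|---|---|
| 2, p<0.05 | 80.90 | 81.30 | 82.78 | 81.45 | 28.72 |
| 4, p<0.05 | 82.60 | 83.85 | 85.15 | 82.72 | 27.42 |
| 6, p<0.05 | 82.70 | 84.45 | 85.78 | 82.60 | 26.75 |
| 4, p<0.20 | 82.12 | 83.70 | 85.05 | 82.88 | 72.50 |

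Fixed adjustment minus chi-square: 1.88, 2.55, 3.08 and 2.93 points. Triggered minus chi-square: 0.55, 0.12, −0.10 and 0.76 points.

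False positives (%) with no true effect:

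| Parity OR, trigger | Chi-square | Parity only | Triggered | Either result significant | Excess over chi-square |
|---|---|---|---|---|---|
| 2, p<0.05 | 5.25 | 5.35 | 5.00 | 5.48 | 0.23 |
| 4, p<0.05 | 4.15 | 4.62 | 4.05 | 4.28 | 0.13 |
| 6, p<0.05 | 4.08 | 5.00 | 3.92 | 4.25 | 0.17 |
| 4, p<0.20 | 4.32 | 4.92 | 4.15 | 4.78 | 0.46 |

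A second simulation (904 per arm, 4000 null trials, four prognostic covariates) gave 5.55% rising to 5.85% with 8 baseline variables, and 4.75% rising to 5.15% with 15. These are excesses of 0.30 and 0.40 points.

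The simulation error of a single 5% rate is √(0.05·0.95/4000) = 0.34 points. The excesses compare methods on the same trials, so they are steadier than that.

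**The case against.** The strongest reply is that the main analysis is not touched. The chi-square comparison is unconditional, it is the test the sample size was built on, and the triggered model is expressly additional. That stands. A reader might infer that the analyst picks the primary model after seeing the groups, so that the primary p-value is data-driven. The text does not say so.

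A reader might also infer that the rule ignores prognosis and adds any variable that differs. It does not: a difference must also be one that might bear on outcome. That filter is undefined and works only after imbalance is seen, so it does nothing for balanced predictors, but it does blunt the charge that weak covariates are let in.

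The sizes also rest on assumptions. The trigger rates need a threshold and a count that the protocol does not give. The false-positive excess arises only if whichever result is significant could be claimed, which nothing in the protocol authorises. The power gain depends on assumed covariate effects, and the planned 80% is met without it. All of this stands.

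Lastly, the covariate list, the threshold and the modelling detail may properly sit in an analysis plan that is not shown. Their absence is not the point here. What remains is the imbalance trigger, which the article states, and which a plan naming covariates regardless of balance would have to contradict.

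Parity being balanced by design does not remove the case for including it. Parity alone added 0.40 to 1.75 points of power. With a parity odds ratio of 4 or 6, the chi-square test that ignores it ran at 4.1% to 4.3% under the null, against 4.6% to 5.0% with parity in the model, which is mildly conservative.

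**Conclusion.** The point holds as a modest one about the supplementary analysis. The rule bases adjustment on chance imbalance, would almost never bring in the stratification factor, and leaves to chance whether a second estimate of the primary outcome exists.

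The size is small. If either result could be claimed, false positives rise by about 0.2 to 0.4 points (0.13 to 0.46 across all settings run). The main loss is roughly 2 to 3 points of power, under the assumed parity and covariate effects, together with discretion that need not be there. That precision would reach the primary conclusion only if the adjusted result were named primary. Neither the primary test nor the sample size is invalid.

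**What to change.** Replace the conditional sentence with a fixed rule along these lines:

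> An analysis adjusted for parity and [closed list of baseline variables, for example maternal age] will be carried out whatever the observed balance between arms. The baseline table is descriptive and will not be used to choose covariates. The [unadjusted / adjusted] result is primary. The adjusted analysis will report a risk difference or risk ratio.

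Points to settle with it:

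- **Timing.** Close the list before any outcome data by arm are examined, which in practice means before the interim analysis planned at 500 births per arm. A milestone defined by unblinding would not suit an unblinded trial.
- **Scope.** Keep the list short and complete. An open clause admitting other predictors would restore the discretion.
- **Which result is primary.** Keeping the unadjusted result matches the sample-size basis; choosing the adjusted one captures the precision. Either is workable if stated in advance.
- **Effect measure.** An adjusted odds ratio answers a different question from 19% versus 14%. A risk difference or risk ratio from the adjusted model keeps to the stated hypothesis.

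The cost is a few sentences. Parity and date of birth are among the details entered at randomisation, and the demographic questionnaire is completed before it, so no new data are needed. The target of 2008 women is unchanged.
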